**Utilisation in private medical services:**

| 1. Did you have any private doctor consultation in the **last 4 weeks (western medicine / Chinese medicine)**? *(If no, go to 2)* | 1.  2. | Yes  No | | | | | | | |
| --- | --- | --- | --- | --- | --- | --- | --- | --- | --- |
|  |  | General  Practitioner | |  | Specialist | |  | Chinese Medicine | |
| a. How many visits? | 1. | visits | | 2. | visits | | 3. | visits | |
| b. How long did you spend for travelling from home to clinic **on average**? | 1. | Min/Hrs | | 2. | Min/Hrs | | 3. | Min/Hrs | |
| c. How much did you spend for travelling from home to clinic? | 1. |  | | 2. |  | | 3. |  | |
| d. How long did you stay in the clinic **on average**? (Waiting time and consultation time) | 1. | Min/Hrs | | 2. | Min/Hrs | | 3. | Min/Hrs | |
| e. How much did you pay for **each visit** (including subsidies from employer or insurance company)? | 1. |  | | 2. |  | | 3. |  | |
| f. Did any person accompany with you to go for visit(s)? Who was that person? (Gender: Male /Female) | 1. | i.  ii. | Yes (M/F) No | 2. | i.  ii. | Yes(M/F)  No | 3. | i.  ii. | Yes (M/F) No |
| g. Did she/he take time off work/ study? | 1. | i.  ii. | Yes (M/F)  No | 2. | i.  ii. | Yes (M/F)  No | 3. | i.  ii. | Yes (M/F)  No |

| 2. Did you get any self medication in the **last 4 weeks**?  *(If no, go to 3)* | 1.  2. | Yes  No | |
| --- | --- | --- | --- |
| How many times did you get self medication and how much did you pay **each time**? | No. of times | | Cost each time ($) |
| 1. Western over-the-counter medicine | 1. | | 2. |
| b. Chinese over-the-counter medicine  (eg. Chinese medical products) | 1. | | 2. |
| c. Chinese herbal medicine  (eg. herbal medicines which require boiling) | 1. | | 2. |
| 1. Others, please specify:_________________ | 1. | | 2. |

| 3. Did you have any private hospitalisation in the **last 6 months**?  *(If no, go to 4)* | 1.  2. | Yes  No |
| --- | --- | --- |
| a How many days of admission? | days | |
| b. How long did you spend for travelling from home to hospital **on average**? | Min/Hrs | |
| c. How much did you spend for travel from home to hospital? | $ | |
| d. How much did you pay for the **last admission** (including subsidies from employer or insurance company)? | $ | |
| e. Did any person visit you during your **last admission**? Who was that person?  (Gender: Male /Female) | 1.  2. | Yes ( M / F )  No |
| f. How many days did she/he take time off work because of visiting you during your **last admission**? | days | |

**Home care cost:**

| 4. Did any person take care of you at home while you’re sick in the last 6 months? If so, who was that person? (Gender: Male/Female) | 1.  2. | Yes ( M / F )  No | | |
| --- | --- | --- | --- | --- |
| 4a. Did she/ he take any time off work/ study to take care of you? If so, how many days? | 1. | Yes | i.  ii. | Work ________days  study ________days |
| 2. | No | | |

**Lifestyle**:

Smoking

| 5. Did/do you have a habit of smoking? *(If no, go to* ***5e****)* | 1.  2. | Yes  No | | | | |
| --- | --- | --- | --- | --- | --- | --- |
| a. Your smoking habit is: | 1. Now have quit already  (former smoker) | | | | 2. Currently smoke occasionally, fewer than one cigarette a day | 3. Currently smoke, at least one cigarette a day |
| b. How long have you quitted smoking? | _____Yr(s) ____ Mth(s) | | | |  |  |
| c. How many cigarettes (past / present) on average did/do you smoke a day? | 1. cigarettes | | | | 2. cigarettes | 3. cigarettes |
| d. How many years did you/have you smoked? | 1. years | | | | 2. years | 3. years |
| e. Are you a passive smoker at home or work? | 1. | Home: | i.  ii. | Yes  No | | |
| 2. | Work: | i.  ii. | Yes  No | | |

Physical Activity & Exercise

| 6. Do you exercise regularly?  *(If no, go to 7)* | 1.  2. | Yes  No | | | | |
| --- | --- | --- | --- | --- | --- | --- |
| a. What type of exercise do you participate in? (You may have more than one answer) | 1.  aerobic exercise | | 2. stretching exercise | 3. walking slowly (level ground) | 4.  Tai chi / yoga | 5.  others: _________ |
| b. How many times do you do each exercise each week? | 1.  times/wk | | 2.  times/wk | 3.  times/wk | 4.  times/wk | 5.  times/wk |
| c. What is the average duration each time? | 1._____min  a. <15 mins  b.15-30 mins  c. >30 mins | | 2._____min  a. <15 mins  b.15-30 mins  c. >30 mins | 3._____min  a. <15 mins  b.15-30 mins  c. >30 mins | 4._____min  a. <15 mins  b.15-30 mins  c. >30 mins | 5._____min  a. <15 mins  b.15-30 mins  c. >30 mins |

**Demographic data:**

| 7. What is your marital status? | 1. Single | | | 2. Married | | | | | | 3. Separated or divorced | | | 4. Widowed | | | | | 5. Refuse to answer | |
| --- | --- | --- | --- | --- | --- | --- | --- | --- | --- | --- | --- | --- | --- | --- | --- | --- | --- | --- | --- |
|  |  | | | |  | | |  | | | | | |  | | |  | | |
| 8. What is the average monthly income of your household from all sources?  $________________ | 1.  Less than $2,000 | 2.  $2,000  |  $3,999 | | | | 3.  $4,000  |  $5,999 | 4.  $6,000  |  $7,999 | | | | 5.  $8,000  |  $9,999 | | | | 6.  $10,000  |  $14,999 | 7.  $15,000  |  $19,999 | | | 8.  $20,000  |  $24,999 |
| 9.  $25,000  |  $29,999 | 10.  $30,000  |  $39,999 | | | | 11.  $40,000  |  $59,999 | 12.  $60,000  or  above | | | | 13.  No income | | | | 14.  Refuse to  answer | 15.  Don’t know | | |  |
|  |  | | | |  | | |  | | | | | |  | | |  | | |
| 9. What is your average monthly income, including all sources?  $________________ | 1.  Less than $2,000 | | 2.  $2,001  |  $5,000 | | | | | | 3.  $5,001  |  $9,999 | | | 4.  $10,000  |  $14,999 | | | | | | 5.  $15,000  |  $19,999 | |
| 6.  $20,000  |  $29,999 | | 7.  $30,000  or  above | | | | | | 8.  No income | | | 9.  Refuse to answer | | | | | | 10.  Don’t know | |

**標準十二題簡明健康狀況調查表-第**二**版**

**說明：這項調查是詢問您對自己健康狀況的了解。此項資料記錄您的自我感覺和日常生活的情況。**

**請在一個方格內填上X號來回答每個問題。如果您不肯定怎樣回答，請按照您的理解選擇最合適的答案。**

**1. 總括來說，您認為您的健康狀況是：**

| 極好 | | 很好 | | 好 | | 一般 | | 差 |
| --- | --- | --- | --- | --- | --- | --- | --- | --- |
| 1 | 2 | | 3 | | 4 | | 5 | |

**2. 下列問題是您日常生活中可能進行的活動。以您目前的健康狀況，您在進行這些活動時，有沒有受到限制？如果有的話，程度如何？**

|  | 有很大限制 | 有一點限制 | 沒有任何限制 |
| --- | --- | --- | --- |
| a. 中等強度的活動，比如搬桌子，使用吸塵器清潔地面，玩保齡球或打太極拳 | 1 | 2 | 3 |
| b. 上幾層樓梯 | 1 | 2 | 3 |

**3. 在過去四個星期裏，您在工作或其它日常活動中，有多少時間會因為身體健康的原因而遇到下列的問題？**

|  | 常常如此 | 大部分時間 | 有時 | 偶爾 | 從來沒有 |
| --- | --- | --- | --- | --- | --- |
| a. 實際做完的比想做的要少 | 1 | 2 | 3 | 4 | 5 |
| b. 工作或其它活動的種類受到限制 | 1 | 2 | 3 | 4 | 5 |

**4. 在過去的四個星期裏，您在工作或其它日常活動中，有多少時間由於情緒方面的原因（比如感到沮喪或焦慮）遇到下列的問題？**

|  | 常常如此 | 大部分時間 | 有時 | 偶爾 | 從來沒有 |
| --- | --- | --- | --- | --- | --- |
| a. 實際做完的比想做的要少 | 1 | 2 | 3 | 4 | 5 |
| b. 工作時或從事其它活動時不如往常細心了 | 1 | 2 | 3 | 4 | 5 |

**5. 在過去四個星期裏，您身體上的疼痛對您的日常工作（包括上班和家務）有多大影響？**

| 毫無影響 | | 有很少影響 | 有一些影響 | | 有較大影響 | | 有極大影響 |
| --- | --- | --- | --- | --- | --- | --- | --- |
| 1 | 2 | | 3 | 4 | | 5 | |

**6. 下列問題是有關您在過去四個星期裏您覺得怎樣和您其它的情況。針對每一個問題，請選擇一個最接近您的感覺的答案。在過去四個星期裏有多少時間：**

|  | 常常如此 | 大部分時間 | 有時 | 偶爾 | 從來沒有 |
| --- | --- | --- | --- | --- | --- |
| a. 您感到心平氣和？ | 1 | 2 | 3 | 4 | 5 |
| b. 您感到精力充足？ | 1 | 2 | 3 | 4 | 5 |
| c. 您覺得心情不好，悶悶不樂？ | 1 | 2 | 3 | 4 | 5 |

**7. 在過去四個星期裏，有多少時間由於您的身體健康或情緒問題妨礙了您的社交活動 (比如探親、訪友等）？**

| 常常有妨礙 | | 大部分時間有妨礙 | | 有時有妨礙 | | 偶爾有妨礙 | | 完全沒有妨礙 |
| --- | --- | --- | --- | --- | --- | --- | --- | --- |
| 1 | 2 | | 3 | | 4 | | 5 | |

**病人自强量表**

參加了共同護理計劃後,您感到以下的情況有何改變?

(請於每行出最適合的答案)

|  | **大為改善** | **有所改善** | **一樣** | **少了** | **不適用** |
| --- | --- | --- | --- | --- | --- |
|  | **2** | **1** | **0** | **0** |  |
| a. 能夠應付生活 |  |  |  |  |  |
|  |  |  |  |  |  |
| b. 能夠了解自己的疾病 |  |  |  |  |  |
|  |  |  |  |  |  |
| c. 能夠面對自己的疾病 |  |  |  |  |  |
|  |  |  |  |  |  |
| d. 能夠保持自己身體健康 |  |  |  |  |  |
|  | **大為增强** | **有所增强** | **無甚改變** | **少了** | **不適用** |
| e. 對自己健康的信心 |  |  |  |  |  |
|  |  |  |  |  |  |
| f. 擁有自助的能力 |  |  |  |  |  |

**整體健康轉變評估問卷**

參加了共同護理計劃後, 您認為您的身體健康情況比之前是 ……

(請出最適合的答案)

| 好了很多 | 好了 | 好了一點 | 一樣 | 差了一點 | 差了 | 差了很多 |
| --- | --- | --- | --- | --- | --- | --- |
| +3 | +2 | +1 | 0 | -1 | -2 | -3 |

多謝您參與研究！

-------------------------------------------------完-----------------------------------------------

**私家醫療服務的使用**

| 1. **在過去四個星期裏，**你有冇睇過私家醫生 (西醫 / 中醫)？  *(如答沒有, 回答問題2)* | 1.  2. | | | 有  沒有 | | | | | | | | | |
| --- | --- | --- | --- | --- | --- | --- | --- | --- | --- | --- | --- | --- | --- |
|  | 1. | 普通科 | | | | 2. | 專科 | | | 3. | 中醫 | | |
| a. 請問你睇過私家醫生幾多次？ | 1. | | | | 次 | 2. | 次 | | | 3. | 次 | | |
| b. 請問你由屋企**平均**要搭幾耐車先到私家診所呢？ | 1. | | | | 分鐘/小時 | 2. | 分鐘/小時 | | | 3. | 分鐘/小時 | | |
| c. 請問你由屋企搭車去私家診所要幾多錢呢？ | 1. | | | |  | 2. |  | | | 3. |  | | |
| d. 請問你睇一次私家醫生**平均**要幾耐？ (包括等候同埋見醫生嘅時間) | 1. | | | | 分鐘/小時 | 2. | 分鐘/小時 | | | 3. | 分鐘/小時 | | |
| e. **每次**求診嘅費用有幾多  (包括僱主或保險公司嘅補貼)？ | 1. | | | |  | 2. |  | | | 3. |  | | |
| f. 有冇人陪你睇私家醫生呢？佢係邊個？  (性別：男/女) | 1. | | i.  ii. | | 有 ( 男/女 )  沒有 | 2. | | i.  ii. | 有 ( 男/女 )  沒有 | 3. | | i.  ii. | 有 ( 男/女 )  沒有 |
| g. 佢有冇請假呢？ | 1. | | i.  ii. | | 有  沒有 | 2. | | i.  ii. | 有  沒有 | 3. | | i.  ii. | 有  沒有 |

| 2. **在過去四個星期裏，**你有冇試過自己買藥食？  *(如答沒有, 回答問題3)* | 1.  2. | 有  沒有 | |
| --- | --- | --- | --- |
| 怎樣處理，幾多次，**每次**幾多錢？ | 次數 | | 每次費用 ($) |
| 1. 西藥成藥 | 1. | | 2. |
| b. 中藥成藥 (例如：牛黃解毒片、銀翹) | 1. | | 2. |
| c. 中草藥 (藥材舖執藥) | 1. | | 2. |
| 1. 其他，請註明：______________ | 1. | | 2. |

| 3. **在過去六個月裏，**你有冇入住私家醫院？  *(如答沒有, 回答問題4)* | 1.  2. | 有  沒有 |
| --- | --- | --- |
| a. 請問你留左幾多日院呢？ | 日 | |
| b. 請問你由屋企**平均**要搭幾耐車先到私家醫院呢？ | 分鐘/小時 | |
| c. 請問你由屋企搭車去私家醫院要幾多錢呢？ | $ | |
| d. **上一次**入住醫院嘅費用有幾多  (包括僱主或保險公司嘅補貼)？ | $ | |
| e. 有冇人係你**上一次**入院時照顧患病嘅你？佢係邊個？ (性別：男/女) | 1.  2. | 有 _____ (男/女)  沒有 |
| f. 係你**上一次**入院時佢請咗幾多日假照顧你？ | 日 | |

**家居照顧**

| 4. **在過去六個月裏，**當你患病嘅時候有冇人照顧你嘅起居飲食？佢係邊個？ (性別：男/女) | 1.  2. | 有 _____ (男/女)  沒有 | | |
| --- | --- | --- | --- | --- |
| 4a. 佢洗唔洗請假照顧你？唔番工定係唔番學？如果要請假，請幾多日呢？ | 1. | 有 | i.  ii. | 唔番工________日  唔番學 ________日 |
| 2. | 沒有 | | |

**生活方式**

吸煙

| 5. 你有冇食煙嘅習慣？*(如答沒有, 回答問題****5e****)* | 1.  2. | | 有  沒有 | | | | |
| --- | --- | --- | --- | --- | --- | --- | --- |
| a. 請問你食煙嘅習慣是： | 1. 現在完全戒煙 | | | | | 2. 現在間中食煙，每日不夠一支 | 3. 現在每日食煙起碼一支 |
| b. 請問你已戒煙有幾耐？ | ___年___ 月 | | | | |  |  |
| c. 請問你(以前 / 現在)平均每日吸多少支煙? | 1. 支 | | | | | 2. 支 | 3. 支 |
| d. 請問你食左幾多年煙？ | 1. 年 | | | | | 2. 年 | 3. 年 |
| e. 不計算你自己，請問你**屋企**同埋**工作範圍**有沒有其他人食煙呢？ | 1. | 屋企: | | i.  ii. | 有  沒有 | | |
| 2. | 工作範圍: | | i.  ii. | 有  沒有 | | |

運動習慣

| 6. 你有冇定期做運動嘅習慣？  *(如答沒有, 回答問題7)* | 1.  2. | 有  沒有 | | | | |
| --- | --- | --- | --- | --- | --- | --- |
| a. 你是參與什麼類型的體育活動(你可選擇多過一個答案) | 1.有氧健身法 | | 2. 舒展運動 | 3. 平路慢步 | 4. 太極/瑜珈 | 5. 其他： _________ |
| b. 每星期做幾多次運動？ | 1. ____ 次 | | 2. _____ 次 | 3._____ 次 | 4._____ 次 | 5. _____ 次 |
| c. 你每次平均做幾耐運動？ | 1._____分鐘  a. < 15 分鐘  b. 15-30分鐘  c. > 30分鐘 | | 2._____分鐘  a. < 15 分鐘  b. 15-30分鐘  c. > 30分鐘 | 3._____分鐘  a. < 15 分鐘  b. 15-30分鐘  c. > 30分鐘 | 4._____分鐘  a. < 15 分鐘  b. 15-30分鐘  c. > 30分鐘 | 5.____分鐘  a. < 15 分鐘  b. 15-30分鐘  c. > 30分鐘 |

----------------------------------------------------完-------------------------------------------------

**SF-12 HEALTH SURVEY (VERSION 2.0)**

INSTRUCTIONS: This survey asks for your views about your health. This information will help keep track of how you feel and how well you are able to do your usual activities.

Answer every question by marking the answer as indicated. If you are unsure about how to answer a question, please give the best answer you can.

1. In general, would you say your health is:

| Excellent | Very good | Good | Fair | Poor |
| --- | --- | --- | --- | --- |
| 1 | 2 | 3 | 4 | 5 |

2. The following questions are about activities you might do during a typical day. Does **your health now limit you** in these activities? If so, how much?

|  | Yes, limited a lot | Yes, limited a little | No, not limited at all |
| --- | --- | --- | --- |
| a. **Moderate activities**, such as moving a table, pushing a vacuum cleaner, bowling, or playing golf | 1 | 2 | 3 |
| b. Climbing **several** flights of stairs | 1 | 2 | 3 |

3. During the **past 4 weeks**, how much of the time have you had any of the following problems with your work or other regular daily activities **as a result of your physical health**?

|  | All of the time | Most of the time | Some of the time | A little of the time | None of the time |
| --- | --- | --- | --- | --- | --- |
| a. **Accomplished less** than you would like | 1 | 2 | 3 | 4 | 5 |
| b. Were limited in the **kind** of work or other activities | 1 | 2 | 3 | 4 | 5 |

4. During the **past 4 weeks**, how much of the time have you had any of the following problems with your work or other regular daily activities **as a result of any emotional problems** (such as feeling depressed or anxious)?

|  | All of the time | Most of the time | Some of the time | A little of the time | None of the time |
| --- | --- | --- | --- | --- | --- |
| a. **Accomplished less** than you would like | 1 | 2 | 3 | 4 | 5 |
| b. Did work or other activities less **carefully** than usual | 1 | 2 | 3 | 4 | 5 |

5. During the **past 4 weeks**, how much did **pain** interfere with your normal work (including both work outside the home and housework)?

| Not at all | A little bit | Moderately | Quite a bit | Extremely |
| --- | --- | --- | --- | --- |
| 1 | 2 | 3 | 4 | 5 |

6. These questions are about how you feel and how things have been with you during the **past 4 weeks**. For each question, please give the one answer that comes closest to the way you have been feeling. How much of the time during the **past 4 weeks**...

|  | All of the time | Most of the time | Some of the time | A little of the time | None of the time |
| --- | --- | --- | --- | --- | --- |
| a. Have you felt calm and peaceful? | 1 | 2 | 3 | 4 | 5 |
| b. Did you have a lot of energy? | 1 | 2 | 3 | 4 | 5 |
| c. Have you felt downhearted and depressed? | 1 | 2 | 3 | 4 | 5 |

7.During the **past 4 weeks**, how much of the time has your **physical health** or **emotional problems** interfered with your social activities (like visiting friends, relatives, etc.)?

| All of the time | Most of the time | Some of the time | A little of the time | None of the time |
| --- | --- | --- | --- | --- |
| 1 | 2 | 3 | 4 | 5 |

**The Patient Enablement Instrument**

As a result of your participation in Shared-Care Programme, do you feel you are….

(please  one box in each row):-

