## Subjects

All patients who have been enrolled into the PEP programme will be included in the evaluation on process of care for each audit cycle; whereas all enrolled subjects who have been recruited for more than 12 months in the programme will be included in the evaluation on the clinical outcomes of care for each audit cycle.

To determine a difference of programme performance and impact between group (PEP participants and non-participants). A cohort of all eligible DM patients under care of HA GOPC at 1 Sep 2009 would be included for the monitoring of the changes in clinical and service utilization outcomes from Sep 2009 to Sept 2015.

550 patients who have enrolled into the PEP and 550 who have not taken part in the PEP will be invited in person from the general outpatient clinics by trained research assistants at the beginning of each evaluation cycle to take part in a telephone survey on patient reported outcomes for each cluster and written consent will be obtained (appendix A). All subjects who have given consent to the telephone follow-up survey will be interviewed by telephone within four weeks, at 6, 12, 36 and 60 months from recruitment to answer the SF-12 Health Survey on quality of life (QOL), the patient enablement Instrument, the Global Rating Scale (GRS) change in health, and a structured questionnaire on private service utilization rates.

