  2. The Patient Enablement Instrument (PEI) is a measure of patient’s enablement in coping with the illness and life (Howie, Heaney et al. 1998). It has 6 items each rated on a 3-point (0, 1, and 2) scale. The summation of the item scores gives the PEI score with a higher score indicating better enablement. The PEI has been translated into Chinese and shown to be valid and reliable in the general Chinese population (Lam, Yuen et al. 2010).
  3. The Global Rating Scale (GRS) is adapted from those used in studies by Jaeschke and Osoba et al (Jaeschke, Singer et al. 1989; Osoba, Rodrigues et al. 1998). It assesses the subject’s subject global perception of any change in the overall health condition on a 7-point scale (-3, -2, -1, 0, 1, 2, and 3) over the six months.

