## Data analysis

1. Descriptive statistics on standard of care will be calculated, including percentage of centers meeting each structure criterion, percentage of subjects enrolled, dropped out, completion of the programme, receiving criterion process, investigations and referral per protocol, and percentage of subjects achieving the criterion outcome.
2. The change in clinical, service, and patient reported outcomes after the PEP programme at baseline, 6, 12, 36 and 60 months will be compared by paired sample t-test. The audit cycle will be repeated annually over a period of 5 years.
3. Independent sample t-test or Chi square test as appropriate will be used to compare the clinical and service utilization outcomes between PEP patients and controls.
4. Independent sample t-test or Chi square test as appropriate will be used to compare the clinical and service utilization outcomes between results in achieved in different audit cycles.
5. Cost effectiveness analysis (CEA) by mathematical modeling will be carried out by using cost and clinical outcome data provided by the HA, as well as quality-of-life and private service utilization cost data collected by the telephone surveys.

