**Global Rating on Change Scale**

How would you rate the change in your health condition after participating in the Shared Care Programme?

| **MUCH BETTER** | **BETTER** | **A LITTLE BETTER** | **SAME** | **A LITTLE WORSE** | **WORSE** | **MUCH**  **WORSE** |
| --- | --- | --- | --- | --- | --- | --- |
| +3 | +2 | +1 | 0 | -1 | -2 | -3 |

-------------------------------------------------end-----------------------------------------------

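### The PEI and GRS follow-up questions name the Shared-Care Programme instead of PEP and presuppose participation, although the protocol also gives them to 550 non-participants

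*Protocol*

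**What the plan says.** **The questions.** In the English follow-up form (Protocol, Appendix D), the PEI begins "As a result of your participation in Shared-Care Programme" and the GRS asks "How would you rate the change in your health condition after participating in the Shared Care Programme". The Chinese PEI reads "參加了共同護理計劃後,您感到以下的情況有何改變" and the Chinese GRS "參加了共同護理計劃後, 您認為您的身體健康情況比之前是"; both name 共同護理計劃, the shared care programme. The title and spoken introduction of the same Chinese follow-up form name 病人自强計劃, which is PEP.

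**Who answers.** The Abstract and the Subjects section recruit 550 PEP participants and 550 non-participants to the telephone survey. Subjects then states: "All subjects who have given consent to the telephone follow-up survey will be interviewed by telephone", and lists SF-12, PEI, GRS and private service use as the content. Data Collection describes the same interviews for the 550 PEP patients only.

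**When.** Data Collection puts SF-12v2 alone at the first interview and adds PEI and GRS at 6, 12, 36 and 60 months. The secondary outcomes list PEI and GRS scores at those four times. A footnote in Appendix C restricts both to 6 months.

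**What GRS measures.** Data Collection defines it as "global perception of any change in the overall health condition on a 7-point scale", over a period of six months.

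**Analysis.** Data analysis item 2 says that changes in clinical, service and patient reported outcomes "at baseline, 6, 12, 36 and 60 months will be compared by paired sample t-test". Item 3 compares PEP patients with controls on clinical and service utilization outcomes only.

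**The concern.** Hypothesis 5 expects improvement in quality of life, enablement and overall health after PEP. PEI and GRS carry the second and third of these. If the question names another programme, a PEP patient may answer about that programme, answer about PEP because the interviewer mentioned it at the start, or decline. The data will not show which.

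For non-participants the difficulty lies deeper than the name. They joined no PEP, so a question about change following participation has no referent. Putting PEP in place of the Shared-Care Programme leaves this unsolved.

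The wording determines what is recorded, so a later analysis plan cannot recover it. The conflicts over who is asked and at which interviews also leave it open how many PEI and GRS values there should be.

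**Working it through.** This is mainly a comparison of passages, with one check of the survey's size.

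**1. Programme name.**

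| Place in Appendix D, follow-up form | Programme named |
| --- | --- |
| Chinese title and introduction | 病人自强計劃 (PEP) |
| PEI, Chinese | 共同護理計劃 (shared care) |
| GRS, Chinese | 共同護理計劃 (shared care) |
| PEI, English | Shared-Care Programme |
| GRS, English | Shared Care Programme |

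The mismatch occurs in both instruments and both languages, so it is not an extraction artefact. The protocol text shown uses the term nowhere else and does not define it as another name for PEP.

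**2. What a non-participant can answer.** PEI items score 2, 1, 0 or 0, plus a not-applicable column without a score. GRS offers seven ratings from +3 to -3 and no not-applicable option. The truthful PEI answer is therefore unscored. Any GRS answer, including 'same', does not rate the change asked about. Appendix D shows one follow-up form, with no separate version for controls.

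**3. Who and when.**

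| Section | Who | PEI and GRS at |
| --- | --- | --- |
| Abstract | both groups | baseline, 6, 12, 36, 60 months (as a general schedule) |
| Subjects | all consenting | first interview, 6, 12, 36, 60 months (as a general schedule) |
| Data Collection | PEP patients | 6, 12, 36, 60 months |
| Secondary outcomes | not stated | 6, 12, 36, 60 months |
| Appendix C | not stated | 6 months only |

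The baseline form in Appendix D contains neither instrument, which supports Data Collection and rules out a baseline score.

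**4. Reference period of GRS.** The gaps between successive follow-ups are 12 - 6 = 6, 36 - 12 = 24 and 60 - 36 = 24 months. A six-month period covers the interval since the previous interview at 6 and 12 months, but not at 36 or 60. The form states no period; it refers to the time since joining a programme.

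**5. Paired test.** Baseline values of PEI and GRS on the forms: 0. A baseline-to-follow-up pair therefore cannot be formed. Pairs between follow-ups exist under Data Collection and the secondary outcomes; under Appendix C there is one measurement per patient and no pair at all.

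**6. Size of the survey.** The plan's figure reproduces. With a standardised difference of 0.3, 80% power and two-sided 5%, n per group = 2 × (1.960 + 0.842)² / 0.3² = 174.4, rounded up to 175, or 350 in total. Allowing for 25% loss at each of four follow-ups, 175 / 0.75⁴ = 553 per group, against 550 stated. From 1,100 recruited, the numbers expected at the four interviews are:

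- 6 months: 1,100 × 0.75 = 825
- 12 months: 1,100 × 0.75² = 619
- 36 months: 1,100 × 0.75³ = 464
- 60 months: 1,100 × 0.75⁴ = 348

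Half of each would be controls under equal loss. This calculation rests on quality of life, so correcting PEI and GRS does not change it.

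**The case against.** Several things weaken the point.

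- **The interviewer supplies context.** The survey is done by telephone and the introduction names PEP, so many participants may understand what is meant. This lowers the risk of misreading but does not remove it, because each question then names something else.
- **No between-group test of PEI or GRS is specified.** Hypothesis 5 can be read as a within-group statement, item 3 of Data analysis leaves patient reported outcomes out, and Data Collection mentions only PEP patients. This stands. A reader might infer that a planned comparison is left with no usable sample; the documents do not support that, because they set out no such comparison. They do collect both instruments in both groups under Abstract and Subjects, and the Abstract's purpose is to evaluate the programme's effect on them.
- **The paired test may not be meant for these scales.** The secondary outcomes distinguish change in SF-12v2 from PEI and GRS scores at follow-up, and a transition rating has no baseline by nature. This also stands: item 2 is loosely worded, and its conflict with the forms is one of wording, not a failed analysis.
- **Respondents can tick a box.** They can, through not applicable on PEI or 'same' on GRS, so it would be too strong to say that controls cannot answer. What they cannot give is an interpretable score.

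**Conclusion.** The point holds in this form: the PEI and GRS questions name the wrong programme in both languages, they do not suit non-participants, and the protocol contradicts itself on who answers them and when.

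It affects two of the three instruments for hypothesis 5. If Subjects is followed, every PEI and GRS question put to a control is affected: about 412 controls at 6 months (550 × 0.75 = 412.5), falling to about 174 at 60 months (550 × 0.75⁴). If Data Collection is followed, no control is asked and only the programme name matters. If Appendix C is followed, only the 6-month interview is involved. These counts assume that the stated 25% loss compounds, that it is equal in both groups, and that 1,100 is the survey total; the wording about each cluster leaves the last open.

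A reader might put the damage at all 1,100 respondents at each of four follow-ups. The protocol's own loss assumption and Appendix C do not support that. Nor do the documents show that PEP patients will in fact rate a different programme, only that they are asked to.

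PEI and GRS are secondary outcomes. The primary outcomes and the SF-12-based sample size are unaffected. The correction is still worth making before follow-up interviews, because it changes the data collected.

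**What to change.** 1. Name PEP in the PEI and GRS questions put to participants, in English and Chinese.
2. Reconcile Abstract, Subjects, Data Collection, the secondary outcomes and Appendix C on whether non-participants answer PEI and GRS and at which interviews.
3. If controls answer, use one neutral question for both groups with a stated reference point, for example since the first interview. A question about the last six months would miss earlier change at the 36- and 60-month interviews. Align the six-month definition of GRS in Data Collection with the reference point chosen.
4. In Data analysis item 2, state that the paired test from baseline applies, among the PRO scales, to SF-12v2, and that PEI and GRS are analysed as follow-up scores, between groups if controls answer.

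The cost is small: two questionnaire pages to reprint in each language, a few sentences in the protocol and a minor ethics notification. The drawback is that a neutral question departs from the current PEI wording. Keeping the PEP-specific question as an extra item for participants meets this, at the price of a slightly longer interview for them.
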